## Abstract

**Background:**

Language recovery is limited in moderate to severe post-stroke aphasia patients. Repetitive transcranial magnetic stimulation (rTMS) has emerged as a promising tool in improving language dysfunctions caused by post-stroke aphasia, but the treatment outcome is as yet mixed. Considerable evidence has demonstrated the essential involvement of the cerebellum in a variety of language functions, suggesting that it may be a potential stimulation target of TMS for the treatment of post-stroke aphasia. Theta burst stimulation (TBS) is a specific pattern of rTMS with shorter stimulation times and better therapeutic effects. The effect of continuous TBS (cTBS) on the cerebellum in patients with aphasia with chronic stroke needs further exploration.

**Methods:**

In this randomized, sham-controlled clinical trial, patients (*n* = 40) with chronic post-stroke aphasia received 10 sessions of real cTBS (*n* = 20) or sham cTBS (*n* = 20) over the right cerebellar Crus I+ a 30-min speech-language therapy. The Western Aphasia Battery (WAB) serves as the primary measure of the treatment outcome. The secondary outcome measures include the Boston Diagnostic Aphasia Examination, Boston Naming Test and speech acoustic parameters. Resting-state fMRI data were also obtained to examine treatment-induced changes in functional connectivity of the cerebro-cerebellar network. These outcome measures are assessed before, immediately after, and 12 weeks after cerebellar cTBS intervention.

**Discussion:**

This protocol holds promise that cerebellar cTBS is a potential strategy to improve language functions in chronic post-stroke aphasia. The resting-state fMRI may explore the neural mechanism underlying the aphasia rehabilitation with cerebellar cTBS.

## Introduction

Aphasia is an acquired language disorder caused by ischemic or hemorrhagic stroke (Engelter et al., 2006), characterized by impairments in verbal fluency, language comprehension, word repetition, and picture naming as well as reading/writing skills. Approximately, one-third of post-stroke patients develops aphasia (Engelter et al., 2006), which persists in approximate 20% of long-term stroke survivors (Berthier, 2005). Patients with post-stroke aphasia suffer from decreased quality of life, limited independence, and substantial long-term disability (Cruice et al., 2011; Ellis et al., 2012). To date, speech-language therapy (SLT) is considered as the standard protocol for the treatment of post-stroke aphasia and produce beneficial effects on language functions, but the effect size is somewhat small that results in modest improvements (Brady et al., 2012). Therefore, it is important to develop other therapeutic approaches to improve the effectiveness of SLT for aphasia treatment.

In recent years, repetitive transcranial magnetic stimulation (rTMS) has emerged as a promising non-invasive neuromodulation method to augment the treatment of post-stroke non-fluent aphasia (Hartwigsen and Saur, 2017; Fisicaro et al., 2019; Ren et al., 2019). Generally, low-frequency rTMS (≤1 Hz) is considered to decrease cortical excitability, while high-frequency rTMS (≥5 Hz) produces the opposite effect (Chen and Seitz, 2001). The majority of recent studies have shown naming improvements in post-stroke non-fluent aphasia by delivering inhibitory low-frequency rTMS over the intact right inferior frontal gyrus (IFG) (the right hemisphere homolog of Broca’s area) (Hara et al., 2015; Harvey et al., 2017; Ren et al., 2019; Kim et al., 2020). Similar beneficial effects on post-stroke aphasia were also observed when excitatory high-frequency rTMS was applied over the left perilesional cortex (Broca’s area) or right intact IFG (Hara et al., 2017; Hu et al., 2018). Alternatively, applying rTMS over other cortical regions is also beneficial for post-stroke aphasia, as evidenced by improvement in speech perception and auditory comprehension following low-frequency rTMS over the right posterior superior temporal gyrus (pSTG) (Kawamura et al., 2019; Ren et al., 2019). Nevertheless, it is noteworthy that the evidence for beneficial effects of rTMS on post-stroke aphasia is not unequivocal (Breining and Sebastian, 2020). Some studies reported null results when low-frequency rTMS was applied over the right hemisphere, showing that rTMS did not add to the effect of SLT on post-stroke aphasia (Santos et al., 2017; Heikkinen et al., 2018). Among many possible resources of the inconsistencies across the studies investigating the efficacy of rTMS for post-stroke aphasia are type of stimulation modality (inhibitory or excitatory), laterality of brain hemisphere (left or right), and choice of stimulation target (Broca’s area, STG, etc.) (Breining and Sebastian, 2020). Particularly, the optimal protocol of rTMS over the right hemisphere remains controversial for aphasia rehabilitation (Anglade et al., 2014), which is due to the limited knowledge about the causal links between cortical brain regions and language functions. Accordingly, developing a novel stimulation protocol with other potential targets that are significantly involved in language processing is important for improving effectiveness of TMS in augmenting the treatment of post-stroke aphasia.

The present study protocol proposes a research protocol that stimulates the right cerebellum with TMS to augment SLT for patients with post-stroke aphasia. Multiple lines of evidence have demonstrated significant contributions of the right cerebellum to a variety of language functions, including word retrieval and generation, verbal working memory, language learning, and semantic processing (Gordon, 1996; Desmond and Fiez, 1998; Murdoch, 2010; Stoodley, 2012; Mariën and Borgatti, 2018). Clinical evidence has shown deficits in a variety of language tasks as a result of damage to the right cerebellum (Marien et al., 1996, 2001; Silveri et al., 1998). Moreover, a growing body of empirical and clinical studies using transcranial direct current stimulation (tDCS) has established a causal link between the right cerebellum and language functions. For example, applying tDCS over the right cerebellum in healthy individuals exerts modulatory effects on various speech/language tasks, such as verbal generation (Pope and Miall, 2012), verbal fluency (Turkeltaub et al., 2016), semantic prediction (D’Mello et al., 2017), and speech motor learning (Lametti et al., 2018). Clinically, several recent studies showed augmentation of SLT in post-stroke aphasia with tDCS over the right cerebellum (Sebastian et al., 2016, 2020; Marangolo et al., 2018). For example, one randomized, double-blind, sham-controlled study found significant improvement in verbal generation in patients with post-stroke aphasia following 4-week cathodal tDCS over the right cerebellum coupled with SLT (Marangolo et al., 2018). In another randomized, double-blind, sham-controlled study (Sebastian et al., 2020), both cathodal and anodal tDCS over the right cerebellum led to improved picture naming in chronic post-stroke aphasia, while greater gains were noted for patients receiving cathodal cerebellar tDCS. Taken together, these studies provide evidence suggesting that the cerebellum may be an optimal site of neuromodulation for the treatment of post-stroke aphasia.

On the other hand, continuous theta burst stimulation (cTBS) is applied over the right cerebellum in the present study protocol. As a specific form of rTMS, cTBS produces an inhibitory effect on cortical excitability for up to 60 min after less than 1-min of stimulation (Huang et al., 2005). In addition to modulating cerebellar activity (Koch, 2010), cTBS over the right cerebellum exerts modulatory effects on speech/language production (Arasanz et al., 2012; Sheu et al., 2019). Cerebellar TBS is safe and tolerable and has reported no serious adverse effects (Hurtado-Puerto et al., 2020). The previous studies have shown that the cerebellar cTBS modulates motor cortical excitability and improves motor symptoms (e.g., gait ataxia and dyskinesia) in a variety of neurodegenerative diseases, such as Parkinson’s disease (PD) and spinocerebellar ataxia (SCA) (Koch et al., 2009, 2014; Benussi et al., 2020; Maas et al., 2020). Moreover, one recent study on patients with SCA showed that single-session c-TBS over the right cerebellum produces facilitatory effects on their abnormalities in auditory-motor integration for vocal pitch regulation (Lin et al., 2022). Therefore, it is plausible to assume that stimulating the right cerebellum with inhibitory cTBS coupled with SLT leads to beneficial effects on chronic post-stroke aphasia, which is yet to be answered.

To this end, the purpose of the present study is to investigate the short- and long-term effectiveness of cTBS over the right cerebellum in augmenting language recovery in chronic post-stroke aphasia in a randomized, sham-controlled design. In addition to aphasia test batteries and speech acoustic analyses for evaluation of treatment outcome, the resting-state functional magnetic resonance (RS-fMRI) is also used to explore the neural mechanisms underlying aphasia rehabilitation. The previous studies have shown associations between improved spelling or phonemic fluency and increased resting-state functional connectivity between the cerebellum and language-related cortical regions for patients with chronic post-stroke aphasia or healthy individuals following tDCS over the right cerebellum (Sebastian et al., 2016; Turkeltaub et al., 2016). Accordingly, we hypothesize that, following cTBS over the right cerebellum, patients with chronic post-stroke aphasia will exhibit improved language functions and increased functional connectivity within the cerebro-cerebellar language network. This randomized, sham-controlled study provides significant new insights into the therapeutic efficacy of cTBS over the right cerebellum to augment SLT for post-stroke aphasia and the underlying neuroplastic mechanisms.

## Methods

### Study Design

This is a prospective, randomized, sham-controlled, single-center study (Registration number: ChiCTR210049828) that will be conducted in the Department of Neurorehabilitation, Wuxi Tongren Rehabilitation Hospital, China. Hospitalized patients with chronic post-stroke aphasia are recruited to participate in the study. They are randomly assigned with a ratio of 1:1 to a real or sham stimulation group. Details about the study design and data collection are shown in Figure 1 and Table 1. On the day of enrollment (T0), after the end of cerebellar cTBS intervention (T1), and 12 weeks post-treatment completion (T2), aphasia test batteries and speech acoustic analyses are performed to evaluate language functions in post-stroke aphasia. Also, RS-fMRI data are collected before and after the end of the intervention. This study has been approved by the Ethics Committee of Wuxi Mental Health Center and Wuxi Tongren Rehabilitation Hospital (WXMHCIRB2021LLky078).

**FIGURE 1 F1:**
[figure not shown]
Flow chart of study procedure. cTBS, continuous theta burst stimulation.

**TABLE 1 T1:** Overview of data collection and study timings.

Study period visits	Pre-enrollment	T0	T1	T2
Relative start of treatment days	−1 week	Day 0	±3 days after intervention	±3 days after 12 weeks of intervention
Screening (in-/exclusion criteria)	×			
Written informed consent	×			
Medical history	×			
Randomization		×		
NIHSS		×		
WAB		×	×	×
BDAE		×	×	×
BNT		×	×	×
Acoustic evaluation		×	×	×
RS-fMRI		×	×	

### Participants

The inclusion and exclusion criteria of the present study correspond to the guidelines for using rTMS in clinics and research (Wassermann, 1998; Rossi et al., 2009; Rossini et al., 2015). Participant inclusion criteria are: (1) patients aged 40–80 years; (2) first-ever unilateral ischemic stroke on the left hemisphere; (3) longer than 6 months post-stroke; (4) non-fluent aphasia as confirmed by the Western Aphasia Battery (WAB); (5) right-handed, native-Chinese speakers without experience of professional vocal or instrumental training; (6) Boston Diagnostic Aphasia Examination (BDAE) Grades I–III; and (7) elementary education level and above, with normal or corrected to normal vision. Participant exclusion criteria are: (1) history of substance or alcohol abuse, premorbid seizures, or neuropsychiatric diseases; (2) contraindications involving TMS and fMRI (e.g., skull defect or skin damage at the stimulation site, intracranial implant, cardiac pacemaker, and implanted drug pumps); (3) history of neurosurgical treatment; (4) unable to cooperate with assessment and treatment due to severe cognitive impairment; and (5) other neurological disease. All participants provide written informed consent prior to participating in the study.

### Sample Size

The sample size was calculated using PASS software (v.15.0) on the basis of previous studies. With an effect size of 0.5 based on the WAB-AQ (Hu et al., 2018), we expect that the target effect size had 80% of power with a type I error of 5% (α = 0.05). Thus, the sample size of each group is at least 16. With an assumption of 20% dropout rate, a sample size of 20 participants will be targeted for each group.

### Randomization and Blinding

Once the inclusion criteria are satisfied, the participant is allocated to one real or sham cTBS group using the network-based random sequence generator to receive real or sham cTBS over the right cerebellum coupled with SLT. Based on the previous studies, patients will receive a 10-day cerebellar cTBS within 2 weeks (Thiel et al., 2013; Wang et al., 2014; Hara and Abo, 2021). The concealment of allocation is performed using sealed envelopes with numbers. The participants and physicians performing the SLT or the data collection/processing are blinded to the grouping. Note that physicians conducting the cTBS intervention cannot be blinded due to the nature of the cTBS intervention and are thus not involved in the research process. The designer and the staff responsible for allocation concealment will not participate in the whole intervention.

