Variability in lesion location and size in brain reorganization for post-stroke aphasia complicate efforts to determine the optimal stimulation strategy at the cortical level (Breining and Sebastian, 2020). Right cerebellar stimulation, in contrast, can potentially serve as a single target site that can be used across patients with post-stroke aphasia with varying site and size of lesion in the left hemisphere (Turkeltaub et al., 2016). The present study proposes a new stimulation protocol for language recovery in chronic post-stroke aphasia by applying inhibitory cTBS over the right cerebellum, since this region has been demonstrated to be essentially involved in a variety of language functions (Gordon, 1996; Desmond and Fiez, 1998; Murdoch, 2010; Stoodley, 2012; Mariën and Borgatti, 2018) and damage to this region leads to impaired language performance (Marien et al., 1996, 2001; Silveri et al., 1998). More importantly, several clinical studies reported improvement in verbal generation or naming functions in the patients with chronic post-stroke aphasia following anodal or cathodal tDCS over the right cerebellum (Sebastian et al., 2016, 2020; Marangolo et al., 2018), providing further evidence in support of the right cerebellum as an optimal stimulation site for neuromodulation in aphasia. On the other hand, Sebastian et al. (2020) found greater beneficial effects on naming functions (relative to sham) when chronic post-stroke patients received cathodal tDCS over the right cerebellum than when they received anodal cerebellar tDCS. And applying inhibitory cTBS over the right cerebellum led to facilitatory effects on impaired vocal motor control in patients with SCA (Lin et al., 2022). As compared to rTMS, cTBS induces robust, long-lasting changes in activation in much shorter periods. Therefore, cTBS over the right cerebellum proposed in the present study protocol may be a promising technique to augment SLT for language recovery in chronic post-stroke aphasia.

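### BDAE severity is known before allocation, but the article states no stratification by it and the phase-by-group model has no severity term, in a trial of 40

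*Protocol article*

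**What the plan says.** Study Design: "They are randomly assigned with a ratio of 1:1 to a real or sham stimulation group". Randomization and Blinding: once the inclusion criteria are met, the patient is "allocated to one real or sham cTBS group using the network-based random sequence generator", and "The concealment of allocation is performed using sealed envelopes with numbers". Neither section mentions blocks, another restriction or a stratification factor. Neither says that the sequence is simple.

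Sample Size: "Thus, the sample size of each group is at least 16", and after the dropout allowance "a sample size of 20 participants will be targeted for each group".

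Participants: eligibility requires "Boston Diagnostic Aphasia Examination (BDAE) Grades I–III". Allocation follows confirmation of eligibility, so the grade is available when the envelope is opened.

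Data Analysis: WAB scores go into an RM-ANOVA with phase (before and after treatment) within subjects and group (real or sham) between subjects. No severity factor or covariate appears.

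**The concern.** Three severity grades are mixed in 40 patients, and severity enters neither the stated allocation nor the stated model. If recovery depends on how severe the aphasia was at entry, a chance difference between arms carries straight into the real-versus-sham contrast in WAB gain. There is a plausible reason for such dependence. Outcome Measures caps the AQ at 100, so the room to improve varies with the starting score. In one small trial, a reader could not separate a stimulation effect from a favourable draw. Precision that a baseline variable already in hand could supply would also be lost.

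**Working it through.** **1. The plan's own figure.** 16 / (1 − 0.20) = 20 per arm, 40 in total. This reproduces.

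**2. Arm sizes, only if the sequence were unrestricted (not stated).** With X ~ Binomial(40, 0.5):
- P(20/20) = C(40,20)/2^40 = 12.5%
- P(24/16 or worse) = 2·P(X ≤ 16) = 26.8%

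Power of a two-sided t-test at α = 0.05 follows. The plan gives "With an effect size of 0.5 based on the WAB-AQ" without naming the measure, so both readings are shown (Cohen's f = 0.5 corresponds to d = 1.0).

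| Split | d = 1.0 | d = 0.5 |
|---|---|---|
| 20:20 | 86.9% | 33.8% |
| 16:24 | 85.5% | 32.7% |
| 14:26 | 83.6% | 31.2% |
| average over all splits | 86.0% | 33.1% |

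Unequal arms cost about 1 point on average and about 3 points at 14:26.

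**3. Severity imbalance, which does not need that assumption.** With exactly 20:20 and no strata, the standardized difference in a baseline measure has SD √(1/20 + 1/20) = 0.316. So P(|difference| ≥ 0.5 SD) = 2·[1 − Φ(0.5/0.316)] = 11.4%.

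Simulation (12,000 trials per setting; assumed: three equally common grades, grade-AQ correlation 0.7-0.9, blocks of 2 and 4 where stratified) gives the share of trials with a baseline AQ gap of at least 0.5 SD:
- simple allocation: about 12%
- fixed 20:20 without strata: 11-12%
- stratified by I versus II-III: about 2-5%
- stratified by all three grades: about 0.1-3%

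A hidden 20:20 list therefore does not help with severity. Only strata do.

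**4. What the stated model removes.** With two phases, the group-by-phase F is the square of the t statistic for the difference in mean change, D.
- If patient i's severity s_i shifts both scores equally, it cancels in post − pre, and D is unaffected.
- If gain = constant + b·s_i + treatment effect, then D = effect + b·(mean s, real − mean s, sham). The second term stays.

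If severity explains a share R² of the variance in change, b in SD units is √R². A 0.5 SD gap then shifts D by 0.5·√R² SD of change: 0.11 at R² = 5%, 0.16 at 10%, 0.22 at 20% and 0.27 at 30%. The documents give no value of R²; this range is assumed.

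**5. Precision.** Adding a severity term with k degrees of freedom to an unstratified 20:20 trial of N = 40 multiplies the variance of the arm effect by about (1 − R²)·[1 + k/(N − k − 3)]. The bracket is 1 + 1/36 = 1.028 for k = 1 and 1 + 2/35 = 1.057 for k = 2.

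| R² | k = 1 | k = 2 | stratified on the same term, about 1 − R² |
|---|---|---|---|
| 5% | 0.976 | 1.004 | 0.95 |
| 10% | 0.925 | 0.951 | 0.90 |
| 20% | 0.822 | 0.846 | 0.80 |
| 30% | 0.719 | 0.740 | 0.70 |

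Simulation agrees within its error. R² here is the share explained by the term as entered, and collapsing grade to two classes loses some of it. Strata plus term give roughly 5-30%. At 20-30% most of this comes from the model term. At 5% the term barely pays for its own degrees of freedom.

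**The case against.** The article condenses a full protocol that is not shown, and sequence type, block size and strata are often left there. A reader might infer from the silence that allocation is one unrestricted sequence and that 20 per arm is left to chance. The text does not support this. A generator with numbered envelopes fits a blocked or fixed 20:20 list, and nothing contradicts the 1:1 ratio. This part of the objection stands in full. The arm-size probabilities are conditional, and the power at stake is small in any case.

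A reader might also cite the Discussion ("Variability in lesion location and size in brain reorganization for post-stroke aphasia complicate efforts") as the plan's own admission of severity imbalance. That sentence concerns lesion site and size as an obstacle to choosing a cortical target, and it is no evidence here.

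It is also fair to say that unstratified randomization is valid, that the pre-treatment score is already a level of the phase factor, and that no passage states that gain depends on severity. The first two are correct. The second disposes only of an additive difference (step 4). The third means the benefit has to be given as a range. A stratum may exist in an unshown document, but the article does state its analysis model, and that model has no severity term.

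**Conclusion.** The concern holds in a limited form. The design does not contradict itself, and its test is not invalid. The stated model leaves severity-dependent gain uncorrected, and unless an unstated stratum exists, a baseline AQ gap of at least 0.5 SD arises in about 11-12% of trials even with equal arms. The consequence rests on an assumption that the documents neither give nor exclude: that severity explains some of the change in WAB-AQ. Over an assumed 5-30%, such a gap moves the arm contrast by 0.11-0.27 SD of change, and strata plus model term lower its variance by roughly 5-30%. At the low end the gain is slight. Arm-size imbalance is secondary and conditional on an unrestricted sequence.

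**What to change.** In Data Analysis, add baseline BDAE grade with its interaction with phase to the primary WAB model for all patients. Entering grade as a covariate in a model of WAB-AQ change is equivalent. This can be done whatever the state of recruitment.

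In Randomization and Blinding, state the sequence type. Where allocation is still open, generate the list as 1:1 permuted blocks of varying size, stratified by screening BDAE grade (I versus II-III), and keep block sizes from recruiting staff. If a restricted or stratified list already exists, say so, keep it, and include its stratum in the model.

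The cost is 1-2 degrees of freedom, two envelope sets, one sentence in each section and slight predictability at the end of a block. No extra patients, visits or tests are needed.

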### Interventions

The application of cerebellar cTBS is administered using Magneuro 100 (Vishee Medical Technology Co., Ltd., Nanjing, China) equipped with a figure 8-shaped coil (7 cm out diameter). Before intervention, a single-pulse TMS will be applied over the right primary motor cortex to determine active motor threshold (AMT). The AMT is defined as the lowest stimulus intensity that produces a motor evoked potential (MEP) of >200 μV in at least 5–10 consecutive trials with 10% maximal voluntary contraction of the first dorsal interosseous muscle of the non-paretic hand (Koch et al., 2020). Each participant receives real or sham cTBS over the Crus I of the right lateral cerebellum (3 cm right and 1 cm inferior to the inion) at 80% of AMT (Lin et al., 2022). A standard cTBS protocol consists of bursts of 3 pulses at 50 Hz that are repeatedly presented at 5 Hz, resulting in a total of 600 pulses in 40 s. The coil is oriented vertically to the target with the handle pointing superiorly during real stimulation; while the stimulation face of the coil is turned 90°, so that the side of the coil is placed on the target during sham stimulation (Rastogi et al., 2017). Immediately following real or sham cerebellar cTBS, all participants receive a 30-min SLT that includes training on comprehension, expression of spoken language, semantic, and phonological processing. The content of SLT will be modified based evaluation of language function on an individual level. Totally, each participant receives 10 sessions of cerebellar cTBS coupled with SLT (5 sessions per week) within 2 weeks.

